## DATA COLLECTION AND ANALYSIS

As a prospective diagnostic accuracy study, reporting will follow the diagnostic accuracy studies (STARD) standard.^17^ The metrics to be included will be sensitivity, specificity, and positive and negative predictive values.

### Sample size justification

TB testing algorithms are tailored by country and target populations; Table 1 gives the number of TB people with TB/number of participants at different prevalence values and different values of precision for 95% confidence interval of point estimate of number of participants with microbiologically confirmed TB identified from each sample population. The sample sizes are chosen to achieve an acceptable level of precision for the estimates of the performance of the both individual TB tests and algorithms. The sample sizes are also suitable for estimating costs and cost-efficiency of the TB test combinations. The calculations in Table 1 have been obtained using the standard Wald normal approximation:$$n_{unadj}=p\cdot \left(1-p\right)\cdot {\left(\frac{z_{\alpha /2}}{E}\right)}^{2}$$where *p* = target proportion (sensitivity in our case; *p* = 0.9), E = target precision (or margin-of-error), and z_a/2_ is the (two-sided) critical value from the normal distribution for significance level a (in our case a = 0.05 and z_a/2_ = 1.96). The resulting number n_unadj_ needs to be adjusted for the TB prevalence, p_TB_ (Table 1 shows both n_unadj_ and n_adj_):$$n_{adj}=\frac{n_{unadj}}{p_{TB}}$$

**Table 1. tbl1:** Sample size calculations for adults to be recruited in Phase 1 of Start4All (the numbers in each cell are n_unadj_/n_adj_ as explained in the sample size calculation equation).

TB prevalence (%)	Precision					
	5%	6%	7%	8%	10%	15%
	Expected number microbiologically confirmed TB cases/number required in sample					
1	139/13,900	97/9,700	71/7,100	55/5,500	35/3,500	16/1,600
2	139/6,950	97/4,850	71/3,550	55/2,750	35/1750	16/800
3	139/4,633	97/3,234	71/2,367	55/1834	35/1,167	16/533
4	139/3,475	97/2,425	71/1775	55/1,375	35/875	16/400
5	139/2,780	97/1940	71/1,420	55/1,100	35/700	16/320
8	139/1738	97/1,213	71/888	55/688	35/738	16/200
9	139/1,545	97/1,078	71/789	55/612	35/389	16/178
10	139/1,390	97/970	71/710	55/550	35/350	16/160
12	139/1,158	97/809	71/592	55/459	35/292	16/133
15	139/927	97/647	71/473	55/367	35/233	16/107
20	139/695	97/485	71/355	55/275	35/175	16/80
27	139/515	97/360	71/263	55/204	35/130	16/60

Populations with predicted low proportions (<10%) of microbiologically confirmed TB (children, CBCF in Viet Nam) will use the same cross-sectional design, but the number of participants with microbiologically confirmed TB may be purposely enriched by inviting individuals attending adjacent centres to the study centres and/or adding intensified FBCF activities (i.e., recruiting inpatients, as well as ambulatory outpatient). Once included in the study, participants will undergo all TB tests under evaluation in the TB test combination. The number of participants to be recruited per country and target population are shown in the Supplementary Material 6 (SM6), further taking into account different levels of expected attrition (due to loss-to-follow-up, unusable data and other causes):$$n_{final}=\frac{n_{adj}}{1-p_{attr}}$$where p_attr_ = expected attrition (expressed as a proportion).

The studies will be analysed individually by countries, and then as a single multi-country evaluation (full details of the model are in Supplementary Material 5). The total sample size to be enrolled varies with the average TB prevalence, target precision, and expected loss-to-follow-up (individuals not completing a diagnostic process) in the individual countries and sites. However, with the assumptions shown in SM6, and assuming an overall proportion of 50% of adult participants being PLHIV, we estimate a sample size of 7,200 PLHIV and 7,200 HIV-negative persons will include at least 548 PLHIV and 548 HIV-negative persons (total 1,096) with a microbiologically confirmed diagnosis of TB. If the recruitment of PLHIV is lower than expected, countries with high burden of HIV-associated TB may enrich recruitment of this population by recruiting in HIV care and treatment clinics and outpatient centres. Similarly, if the TB prevalence amongst study recruits falls below that listed in SM6, countries may adjust case finding activities or focus eligibility criteria to enrich for the recruitment of people with TB.

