### Study participants

Adults will be recruited from lowest level health care facilities (primary health care and district hospitals) across all countries and CBCF in Bangladesh, Cameroon, Nigeria, and Viet Nam. Adults are categorised as 15 years of age and above in Bangladesh, Cameroon, Kenya, Nigeria, and Viet Nam and 18 years of age and above in Brazil and Malawi. Children will be recruited from health care facilities (primary health care and district hospitals) from Cameroon and Viet Nam. Children are categorised as 1–14 years inclusive.

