### Community-based case finding

In Bangladesh, Cameroon, Nigeria, and Viet Nam, adults will be consecutively recruited through CBCF initiatives. Based on local context, CBCF will be conducted in informal urban settlements in Bangladesh, rural communities in Cameroon, and amongst nomadic and internally displaced populations in Nigeria and urban low-income communities in Viet Nam. The CBCF will be organised through lung health camps. There will be community sensitisation drives before the health camps to invite people to participate in the camp. All individuals who are interested in being evaluated for lung disease attending the camp will be screened upon contact by both W4SS, under the same parameters as in health care facilities, and by CXR. A posterior-anterior (PA) X-ray will be taken from all individuals and interpreted by CAD software (qXR, Qure.ai, Mumbai, India). Any individuals that have a CAD software abnormality score of ≥0.3, living with HIV and/or a household contact will be eligible for study entry irrespective of symptoms. The threshold of ≥0.3 has been selected based on previous work conducted within our study countries for CBCF activities.^15^

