Conducting this evaluation across diverse epidemiological and programmatic contexts presents challenges. Variations in HIV prevalence, health care infrastructure, and workforce capacity may influence diagnostic performance and operational feasibility. Start4All mitigates these limitations through rigorous quality assurance procedures, structured training, and cross-country coordination, ensuring consistency in implementation. While experimental test results are not used for clinical management in Phase 1, this design safeguards methodological integrity and provides the evidence foundation for future work. Start4All supports the broader goal of accelerating progress toward universal access to TB diagnosis and care, and ending TB as a public health threat by 2035. It is anticipated that the outcomes from this study will provide policymakers, implementers, and global health partners with a robust evidence base to guide the rational integration of novel diagnostic technologies into TB screening and diagnostic algorithms.

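### One Table 1 cell is wrong (35/738 should be 35/438), and the table's precision holds only if participants are sampled independently of facility and camp

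*Protocol article*

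**What the plan says.** All references are to the protocol article.

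**Sizing.** Under Sample size justification, "The calculations in Table 1 have been obtained using the standard Wald normal approximation". The inputs are a "target proportion (sensitivity in our case", set at 0.9), a margin E ("E = target precision (or margin-of-error")) and z = 1.96 for a two-sided 5% level. The case count n_unadj is divided by TB prevalence to give n_adj, and n_adj by one minus expected attrition to give n_final. The text then says that the total varies with prevalence, target precision and loss to follow-up. It mentions no design effect, ICC or number of sites.

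**Recruitment.** Under Study participants: "Adults will be recruited from lowest level health care facilities (primary health care and district hospitals) across all countries and CBCF" in four named countries. Under Community-based case finding: "The CBCF will be organised through lung health camps". Recruitment is consecutive in both settings.

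**Analysis.** "The studies will be analysed individually by countries, and then as a single multi-country evaluation", with the model placed in Supplementary Material 5. Targets by country and population are in Supplementary Material 6. Neither supplement is shown here.

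**Variation.** The CONCLUSIONS section says: "Variations in HIV prevalence, health care infrastructure, and workforce capacity may influence diagnostic performance and operational feasibility".

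**The concern.** Table 1 is the only place in the article where a reader can see how many participants buy how much precision, so a wrong cell matters if any target was read from it. The printed 738 is also impossible on the table's own logic. It exceeds the 688 required for the tighter 8% precision in the same row, and the 700 required at the lower 5% prevalence in the same column.

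The second issue is what the precision columns mean. People seen at one facility or camp share staff, equipment, specimen handling and referral pattern, so their test results may be correlated given disease status. The article's stated aims (policy use and external validity) reach beyond the enrolled sites. For inference of that kind, variation between sites adds to the uncertainty, and a given number of TB cases carries less information than the same number drawn independently. Accuracy by country and setting is the main product of Phase 1 and informs which algorithms go to Phase 2, so the stated precision should carry its condition.

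**Working it through.** **1. Reproduce the case counts.** n_unadj = 0.9 × 0.1 × (1.96/E)², rounded up.

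| E | Computed | Rounded up | Table 1 |
|---|---|---|---|
| 5% | 138.30 | 139 | 139 |
| 6% | 96.04 | 97 | 97 |
| 7% | 70.56 | 71 | 71 |
| 8% | 54.02 | 55 | 55 |
| 10% | 34.57 | 35 | 35 |
| 15% | 15.37 | 16 | 16 |

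All six agree exactly, which confirms that the design effect built in is 1.

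**2. Reproduce the participant counts.** n_adj = n_unadj / prevalence. All cells agree to within rounding except one. At 8% prevalence and 10% precision, 35/0.08 = 437.5, rounded up to 438, against 738 printed. The excess is 738 − 438 = 300 participants (300/438 = 0.685, about 68%).

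**3. Precision with clustering.** The article gives neither the ICC nor the number of sites, so both are assumptions here, as is equal site size. With m = TB cases per site:

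- design effect DEFF = 1 + (m − 1) × ICC
- half-width = 1.96 × √(0.09 × DEFF / n_unadj)

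Example: 139 cases over 5 sites give m = 27.8. With ICC 0.05, DEFF = 1 + 26.8 × 0.05 = 2.34, and the half-width is 1.96 × √(0.09 × 2.34/139) = 7.6%.

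| Cases (nominal precision) | ICC | 5 sites | 10 sites | 20 sites |
|---|---|---|---|---|
| 139 (5%) | 0.01 | 5.6% | 5.3% | 5.1% |
| 139 (5%) | 0.05 | 7.6% | 6.4% | 5.7% |
| 55 (8%) | 0.01 | 8.3% | 8.1% | 8.0% |
| 55 (8%) | 0.05 | 9.7% | 8.8% | 8.3% |

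**4. Same check by cases per site.** For the 7% column (71 cases):

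- m = 3, ICC 0.01: DEFF 1.02, half-width 7.05%.
- m = 10, ICC 0.05: DEFF 1.45, half-width 8.40%.
- m = 20, ICC 0.10: DEFF 2.90, half-width 11.88%.

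With ICC = 0, Table 1's precision stands.

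**5. Specificity.** Table 1 is sized on sensitivity, but specificity is also a reported metric, and each site supplies many more people without TB than with it. As an illustration, assume specificity 0.70, 688 participants at 8% prevalence (688 − 55 = 633 without TB) and 5 sites, so m = 126.6. Under independence the half-width is 1.96 × √(0.21/633) = 3.6 points. With ICC 0.01, DEFF = 1 + 125.6 × 0.01 = 2.26 and it becomes 5.4 points. A small ICC therefore matters more for specificity than for sensitivity.

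**The case against.** **The size is unknown.** Nothing in the article favours 5 sites over 20, and with many sites and a small ICC the loss for sensitivity is trivial. This stands. The figures above are a range, not an estimate.

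**Sites may be fixed strata.** If the target is average performance over the enrolled sites only, differing site sensitivities do not inflate the variance, because Σ nᵢpᵢ(1 − pᵢ) is at most n·p(1 − p). This also stands. The inflation needs sites to represent a wider population. The article's stated policy use and external validity suggest such a reading, but it does not define the target population of sites.

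**The article does not say that performance differs between sites.** The CONCLUSIONS sentence says only that variation may influence performance, and in context it can be read as variation between countries, which are analysed separately. It makes the independence assumption worth stating; it does not refute it.

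**A stronger reading is tempting.** A reader might infer that the reported 95% intervals will be too narrow. Intervals that ignored site would cover about 80% in the case of 139 cases, 5 sites and ICC 0.05. The document does not support that inference: the Wald formula is given for Table 1 only, and the analysis model is in Supplementary Material 5, which may handle site. Nor can one infer that primary care and district hospital patients are merged into a single country estimate, since Study description and objectives plans evaluation by country and setting.

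**The wrong cell may be harmless.** It overstates the requirement, and nothing shows that a target used it. The pooled planning figures imply 1,096/14,400 = 7.6% prevalence, close to the 8% row, but targets are set by country and population. That justifies a check, not a claim that recruitment was mis-sized.

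**Conclusion.** The cell error is certain: by the article's own formula, 35/738 should read 35/438. Whether it affected any target cannot be seen without Supplementary Material 6.

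The clustering point holds in conditional form. The sizing chain treats TB cases as independent, so Table 1's precision applies under independent sampling. It is optimistic if performance varies between sites and the results are to apply beyond them. Over the assumed ranges (3 to 20 cases per site, ICC 0.01 to 0.10), DEFF runs from 1.02 to 2.90, and a nominal 7% becomes anything from 7.05% to 11.9%. To say flatly that the stated precision will not be achieved would go further than the document allows. No analysis error can be asserted either.

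**What to change.** 1. Correct the 8% prevalence, 10% precision cell to 35/438, and check that no target in Supplementary Material 6 was taken from 738.
2. Keep the planned sample size. Label Table 1 as precision under independent sampling, and add the precision expected at the actual number of facilities and camps for assumed ICCs such as 0.01 and 0.05, using the DEFF formula above. Do the same for specificity, with m as the number of people without TB per site.
3. Confirm in the analysis model that the by-country and by-setting intervals account for site or camp, with a small-cluster correction where sites are few. If sites are instead to be treated as fixed, say so and limit the inference to them.

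The cost is a corrected table, a few added lines and a site or camp identifier for each participant. No extra participants or procedures are needed. The downside is a somewhat less favourable stated precision.

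### Table 1 prints a required sample of 738 at 8% TB prevalence and 10% precision; the plan's own formula gives 438

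*Protocol article*

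**What the plan says.** The protocol article, under Sample size justification, sizes the study for the precision of a sensitivity estimate. It states that "The calculations in Table 1 have been obtained using the standard Wald normal approximation". The inputs are the "target proportion (sensitivity in our case; *p* = 0.9"), a two-sided level ("in our case a = 0.05 and z_a/2_ = 1.96") and "E = target precision (or margin-of-error"). The resulting number of TB cases, n_unadj, is divided by TB prevalence to give the number of participants, n_adj. The caption of Table 1 says that every cell shows these two numbers in that order.

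The row for 8% prevalence, with precision columns of 5, 6, 7, 8, 10 and 15%, reads "139/1738 97/1,213 71/888 55/688 35/738 16/200".

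Attrition is not part of Table 1. The same section applies it afterwards, saying that the numbers per country and population in Supplementary Material 6 are obtained by "further taking into account different levels of expected attrition", through n_final = n_adj/(1 − p_attr).

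**The concern.** The fifth entry in the 8% row does not fit the entries around it. A looser margin of error should need fewer people, yet the requirement rises from 688 at 8% precision to 738 at 10% precision. A higher prevalence should also need fewer people, yet in the 10% precision column the requirement rises from 700 at 5% prevalence to 738 at 8%. Neither can happen when n_adj is n_unadj divided by prevalence.

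This is a required-sample figure in the table that presents the adult sample size calculations, and n_adj is the quantity that the attrition formula takes as its input. If a population had been sized from this cell, its target would be 300 too high before attrition, and its expected case count and margin of error would not match its sample size.

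**Working it through.** **Inputs**, all from Sample size justification: p = 0.9, z = 1.96, E = the column heading, p_TB = the row heading.

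**Step 1: cases needed.** n_unadj = p(1 − p)(z/E)², rounded up.

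| E | Unrounded | Rounded up | Printed |
|---|---|---|---|
| 5% | 138.30 | 139 | 139 |
| 6% | 96.04 | 97 | 97 |
| 7% | 70.56 | 71 | 71 |
| 8% | 54.02 | 55 | 55 |
| 10% | 34.57 | 35 | 35 |
| 15% | 15.37 | 16 | 16 |

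All six columns reproduce, including the 35 in the disputed cell.

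**Step 2: participants needed at 8% prevalence.** n_adj = n_unadj/0.08.

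| E | Computed | Printed |
|---|---|---|
| 5% | 1,737.5 | 1738 |
| 6% | 1,212.5 | 1,213 |
| 7% | 887.5 | 888 |
| 8% | 687.5 | 688 |
| 10% | **437.5** | **738** |
| 15% | 200 | 200 |

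The other entries that end in a half are rounded up, so the cell should read 438. The same calculation over all 72 cells gives agreement within one participant in 71. This cell is the only failure.

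**Step 3: size of the discrepancy.** 738 − 438 = 300. Relative to 437.5 the excess is 300.5/437.5 = 68.7%; relative to 438 it is 300/438 = 68.5%.

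**Step 4: the pair is inconsistent within itself.** 35/738 = 4.7% prevalence, not 8%. Conversely, 738 people at 8% prevalence would yield 738 × 0.08 = 59 cases, and the Wald margin would be 1.96 × √(0.09/59.04) = 0.0765, about ±7.7 points instead of ±10.

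**Step 5: could another convention give 738?**

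- Unrounded n_unadj: 34.57/0.08 = 432.
- One-sided 5% level: 304.
- Continuity correction: about 550 to 557.
- Attrition already included, at assumed values of 5% to 40%: 437.5/0.95 = 461 up to 437.5/0.60 = 729.
- 99% interval: 746. This is close by coincidence, but it conflicts with the stated level of 0.05, with the 35 printed in the same cell and with every other cell.

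None reproduces 738 consistently with the stated method.

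**The case against.** The arithmetic is not open to serious dispute. A fault in reading the table from the PDF cannot be strictly excluded, but nothing points to one: the row and columns are intact and every neighbouring cell matches the formula.

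The strong objection concerns consequence. Table 1 is a grid over prevalence and precision, not a list of targets. The targets are in Supplementary Material 6, which is not shown, and they may have been computed from the formula and not read from the printed grid. Nothing shown says that any population was planned at 8% prevalence with 10% precision. The error also runs in the conservative direction, and it is easy to spot because the value is out of order in both its row and its column. All of this stands.

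A reader might infer that the row matters especially because the plan's overall adult yield is 1,096/14,400 = 7.6%, close to 8%. The documents do not support that inference. A pooled average across countries and settings does not show which row any one population used. If the 14,400 already includes attrition, the implied prevalence is higher: 1,096/(14,400 × 0.90) = 8.5% at an assumed 10% attrition and 1,096/(14,400 × 0.80) = 9.5% at an assumed 20%. The same section also names only children and community-based case finding in Viet Nam as populations expected to fall below 10%, and Table 1 covers adults. If that list is complete, at most one adult population could lie in the 8% row, and nothing shows that it does.

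**Conclusion.** The cell is wrong as printed. Under the plan's own method it should be 35/438; it is overstated by 300 participants, about 69%. The pattern fits a single wrong first digit. The conclusion rests only on the formula and inputs printed beside the table, and 71 of the 72 cells confirm that reading of the method.

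The point stops there. Because the error overstates the requirement, it costs no precision and would not cause under-recruitment. A reader might go on to conclude that recruitment targets, or the totals of 14,400 participants and 1,096 cases, are inflated. The text shown does not establish this, because no target is linked to this cell and Supplementary Material 6 is not available to check.

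**What to change.** Change the Table 1 cell at 8% prevalence and 10% precision from 35/738 to 35/438, and confirm that no target in Supplementary Material 6 was derived from 738.

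Only if one was, choose between two corrections. Either restate that target as 438/(1 − p_attr), or keep the sample size and restate what it delivers: about 59 expected cases and a margin of about ±7.7 points, before attrition.

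The cost is one table cell and one look-up, with no extra participants or data. If a target did come from 738, one stated target or precision figure would also have to be restated.

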### Data collected using electronic CRFs

Study data will be collected using electronic case report forms (eCRFs) developed in REDCap,^18,19^ a secure, web-based platform designed and maintained by the Global Health Trials Unit (GHTU). The Databases were designed with built-in range checks, branching logic, and required fields to minimise entry errors and ensure completeness. Paper CRFs were available as an option. Of the eight implementing partners, five will use the REDCap databases designed and hosted by GHTU, two will use REDCap databases built and hosted in-country with the support of data dictionaries supplied by GHTU to ensure uniformity in field and variable naming, and country partners will use a locally developed and locally hosted data collection software,^20^ with data being transferred to GHTU for bulk upload into the central REDCap database. Quantitative data will be captured for all enrolled participants, including demographic characteristics, medical history, clinical examination findings, and results from diagnostic tests. Laboratory data, including microbiological reference standard results, will be entered into separate eCRFs. All digital CXR image files will be linked to anonymised study IDs, processed and stored separately from the study data. Data entry will be performed by trained study nurses, community health workers, and laboratory staff at participating sites across Bangladesh, Brazil, Cameroon, Kenya, Malawi, and Viet Nam. Data will be entered in real time where possible. Local study teams will perform routine checks, and the GHTU team will conduct centralised monitoring and data validation. All records will be linked to unique participant identifiers, with personal identifiers stored separately from study data to preserve confidentiality.

